#### **3.2. Secondary objective(s)**

The secondary objectives are:

- to characterize the evolution of fetal and neonatal cardiac variability parameters (linear and non-linear analysis, see Appendix 1) in a population of premature babies with and without histological chorioamnionitis. to test the hypothesis that the other parameters for analysing fetal cardiac variability can constitute, alone or in association, in particular with the index of episodes of high variation, a uni or multivariate indicator of histological chorioamnionitis in preterm premature babies.

### **4. DEFINITION OF ELIGIBLE SUBJECTS**

#### **4.1. Inclusion criteria**

The inclusion criteria are:

- adult patient
- singleton pregnancy
- PROM occurring between 26- and 34-weeks' gestation, authenticated on clinical examination and, if in doubt, confirmed by a vaginal diagnostic test detecting IGFBP-1.
- patient who has received information about the protocol and has not expressed opposition to participating.

#### **4.2. Non-inclusion criteria**

The criteria for non-inclusion are:

- multiple pregnancy
- neonatal hypotrophy (birth weight <10th AUDIPOG percentile)
- active maternal smoking
- gestational or pre-pregnancy diabetes
- maternal pathology:
  - o congenital or acquired heart disease

- pulmonary embolism under treatment
- pulmonary arterial hypertension
- moderate to severe chronic renal failure
- Chronic obstructive pulmonary disease
- Autoimmune diseases (systemic lupus erythematosus, multiple sclerosis, Gougerot-Sjögren syndrome)
- fetal malformation with known cardiac, neurological or genetic abnormality

#### **4.3. Exclusion criteria for the main objective**

Delivery within 48 hours of PROM (clinical situation not allowing calculation of the index of episodes of high variation or modelling of changes in HRV analysis parameters).

### **5. JUDGING CRITERIA**

#### **5.1. Primary criterion**

The primary criterion is the effectiveness indicator (area under the ROC curve, sensitivity, specificity, positive predictive value, negative predictive value) of the index of episodes of high variation for the detection of histological chorioamnionitis in preterm PROM.

#### **5.2. Secondary criteria**

- The performance of the approach will also be tested by the changes observed in the parameters of fetal and neonatal cardiac variability (linear and non-linear analysis). The quantitative expression (statistical analysis) and modelling (graphical and statistical analysis) of the evolution of these markers will enable us to define their diagnostic value for the diagnosis of histological chorioamnionitis and/or maternal-fetal infection in preterm PROM.
- an efficiency indicator (area under the ROC curve, sensitivity, specificity, positive predictive value, negative predictive value) will also be used to assess the diagnostic value of the other HRV analysis parameters selected in the form of either a univariate or multivariate indicator for the detection of histological chorioamnionitis in preterm PROM.

### **6. IDENTIFICATION OF THE MEDICAL DEVICE**

Doppler recording of the FHR signal will be carried out using an F3 Fetal Monitor cardiotocograph (EDAN Instruments, Inc; figure 1), which has the same technical features as all competing cardiotocographs. This device has the advantage of being equipped with a 60-hour internal memory, enabling recordings to be stored in the form of independent TRC (Trace File) files, which can be transferred to a computer via a USB port. These TRC files provide a digital record of the fetal heartbeats, resampled at 4 Hz, which can be used to calculate HRV parameters using Matlab® (Mathworks Inc.).

The neonatal cardiac signal will be collected by ECG, 48 hours after birth, then once a week using ECG signal extracts from the polygraph monitor: raw and resampled series at 4 Hz of successive beat-to-beat series (RR), QRS and P morphology axis.

[figure not shown]

Figure 1: F3 Fetal Monitor cardiocotograph (EDAN Instruments, Inc)

## 7. RESEARCH DESIGN

### 7.1. Research methodology

Multicenter observational case-control study with blinded analysis of nursing staff.

### 7.2. Research process

Inclusion will be prospective: any pregnant patient with a singleton pregnancy hospitalized for PROM between 26- and 34-weeks' gestation will potentially be included in the study.

Doppler recording of the FHR signal will be prospective from inclusion, as part of the routine of fetal well-being monitoring. Analysis of HRV parameters (index of episodes of high variation, linear and non-linear analysis) will be carried out using Matlab® software without the knowledge of the nursing staff. The algorithms for calculating these parameters have already been developed by the Signal and Image Processing Laboratory.

Clinical data will be collected prospectively in a relational events database. It will cover maternal, placental and neonatal data.

The Doppler data from the FHR signals, anonymized beforehand, will be stored progressively on a computer dedicated to the study. A copy of the signals acquired will be made regularly on the CIC-IT's secure server via the ASCENT system (Anonymized System for Clinical experimentation: <https://ascent.univ-rennes1.fr/>) and stored progressively on a database dedicated to the study.

In addition, a joint protocol has been drawn up with the investigating centres, setting out in particular the procedures for fetal heart rate recordings. This protocol does not significantly modify the current practices established in these centres, which are already harmonized.

#### Selection of participants

Patients will be selected from the gynecology and obstetrics departments of the University hospitals of Rennes, Angers, Nantes and Poitiers.

### Inclusion visit (=D0)

Its purpose is to present the objectives of the study to the patient, to check the inclusion and non-inclusion criteria and to obtain the patient's non-opposition.

The following data are collected during this visit:

- maternal clinical data
  - o Age
  - o Height and weight with calculation of body mass index
  - o Precise pregnancy dating (obstetric ultrasound performed between 11 WA + 1 day and 14 WA + 6 days)
  - o Obstetrical history: parity, previous obstetrical pathology (preterm PROM, preeclampsia, intrauterine growth retardation, premature delivery), mode of delivery (vaginal delivery, instrumental vaginal delivery, caesarean section).
  - o Term of premature rupture of the membranes and colour of the amniotic fluid
- fetal data
  - o Initial computerized FHR

### RPM – birth

The following data is collected during these visits:

- maternal data:
  - o biological data: leucocyte counts, CRP assays, results of bacteriological vaginal swabs, clinical data: body temperature, colour of amniotic fluid, etc.
  - o date and time of CELESTENE® injections
  - o Initiation of tocolysis (ADALATE®, TRACTOCILE®): method of administration, dates and duration of treatment(s)
- Antibiotic therapy: antibiotic(s), dates and duration of treatment(s)
- fetal data:
- FHR: saved on the monitor, transferred weekly via a USB key and sent via the Internet to the Signal and Image Processing Laboratory (LTSI-UMR INSERM 1099) via the secure ASCENT site (<https://ascent.univ-rennes1.fr/>).
- Oligohydramnios or anamnios

### Birth

The following data are collected during this visit:

- mode of delivery and reason (in particular, suspicion of clinical chorioamnionitis) except if spontaneous labour: spontaneous labour, induction, emergency caesarean section
- context of onset of labour: maternal fever, changes in amniotic fluid, uterine contractions, abnormalities in the FHR (visual or computerized)
- Mode of delivery: vaginal delivery, instrumental vaginal delivery, caesarean section

- Birth weight (expressed in absolute value and percentile according to AUDIPOG reference curves)
- Arterial pH and lactates at the umbilical cord, base excess, PCO2,
- How the child is discharged (resuscitation, routine care, intensive care, post-natal care)
- Neonatal death: date, time and autopsy result if performed

Post-natal period (2 days to 15 weeks)

The following data are collected during this period:

- within 72 hours of birth:
  - neonatal biological data: CRP (all), Procalcitonin, peripheral bacteriological samples and blood cultures, blood glucose (random)
  - neonatal clinical data :
    - respiratory: surfactant, ventilation methods
    - cardiovascular: PAH, use of vasopressin amines
    - blood: anaemia (haemoglobin), jaundice (asat, alat, direct and conjugated bilirubin)
    - assessment of suspected maternal-fetal infection: definite, probable or possible according to the criteria of the National Institute for Health and Care Excellence (NICE guidelines CG149)
    - digestive/hepatobiliary: ulcerative enterocolitis with modified Bell stage
  - cardiac variability data: storage of the neonatal ECG (1 recording of one hour in the first 48 hours, then once a week until discharge from hospital)
- remotely:
  - anatomopathological examination of the placenta using a standardized grid to collect information for identifying chorioamnionitis (25,26)
    - acute chorioamnionitis (maternal inflammation)
      - stage 1: infiltrate of neutrophils (PNN) in the roof of the interventricular chamber
      - stage 2: stage 1 + PNN infiltrate in the chorionic plate
      - stage 3: stage 2 + necrosis of PNN and/or amniotic cells
    - foetal inflammatory reaction
      - stage 1: vessels of the chorionic plate and/or umbilical vein
      - stage 2: stage 1 + umbilical artery
      - stage 3: stage 2 + diffusion in Wharton's jelly
    - presence of placental infarcts (old and/or recent) with percentage of placental surface affected (<10%, between 10 and 30%, >30%)
    - presence of a retroplacental hematoma
    - presence of a marginal decidual hematoma
  - assessment of neonatal cerebral pathologies (results of cerebral imaging: ETF and MRI)

| Actions                           | D0
(Inclusion visit on admission) | Free interval RPM/birth
(RPM at 15 weeks) | Birth | Post-natal period
(neonatology followed by a maximum of 15 weeks) |
|------------------------------------------|---------------------------------------------|-----------------------------------------------------|--------------|-----------------------------------------------------------------------------|
| Signature of no objection                | X                                           |                                                     |              |                                                                             |
| Inclusion fax                            | X                                           |                                                     |              |                                                                             |
| Maternal-fetal clinical data             | X                                           | X                                                   |              |                                                                             |
| Collection of computerized FHR           | X                                           | X                                                   |              |                                                                             |
| Neonatal clinical data                   |                                             |                                                     | X            | X                                                                           |
| Pathological examination of the placenta |                                             |                                                     |              | X                                                                           |
| ECG collection                           |                                             |                                                     | X            | X                                                                           |

## 8. NUMBER OF SUBJECTS REQUIRED

The prevalence of histological chorioamnionitis during preterm PROM is 20 to 30% in the literature (1,10). Given that the mean of the index of high variation episodes (appendix 2, table 1) is in absolute value 3.82 in the case of chorioamnionitis and 1.18 in the absence of chorioamnionitis with a common standard deviation of 1.7, a sample of 60 analysable patients has a power of 95% to detect a significant difference in two-sided formulation and using a Student's t-test with a significant p less than 0.05 based on a prevalence of 15% of histological chorioamnionitis. Given the exclusion criterion for the analysis of the primary objective (delivery within 48 hours of the PROM, which concerns 50% of preterm PROM), a sample of 120 patients is required, 60 of whom can be analyzed for the primary objective.

Taking into account a safety margin of 30% (refusal to participate or presence of non-inclusion criteria), this study requires a minimum potential inclusion of 160 patients.

The planned recruitment is realistic. The annual numbers of pre-term POM at the CHU de Rennes, Angers, Nantes and Poitiers can be estimated at 100, 100, 100 and 60 respectively.

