## 9. STATISTICAL ANALYSIS

The predictive capacity of the index of episodes of high variation and the uni/multivariate indicator obtained from HRV parameters will be estimated on the basis of sensitivity, specificity, false-positive and false-negative rates, and the area under the ROC curve.

An exploratory univariate analysis of the parameters used to analyse HRV will be carried out. Comparisons of the distributions, means and medians of these parameters in the monitoring blocks associated with histological chorioamnionitis and in the blocks not associated with histological chorioamnionitis will be carried out (Student's *t* test and Mann-Whitney test).

Changes over time in the various parameters measured will be compared between the two populations using a 2-factor repeated time ANOVA (gestational age and chorioamnionitis). The subject effect will be included in the model to take account of the matched nature of the measurements.

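### Section 8 justifies 60 analysable patients by a t-test on the mean index rather than by the diagnostic accuracy measures of the primary criterion, and its 95% power does not follow from its own inputs (97 to 99%)

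*Protocol*

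**What the plan says.** Protocol section 3.1 sets an estimation aim: to measure the diagnostic value of the high-variation index for histological chorioamnionitis. Section 5.1 turns this into the endpoint: "The primary criterion is the effectiveness indicator (area under the ROC curve, sensitivity, specificity, positive predictive value, negative predictive value) of the index".

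Section 8 justifies the sample size differently. It states that the mean index "is in absolute value 3.82 in the case of chorioamnionitis and 1.18 in the absence of chorioamnionitis", takes 1.7 as the SD in both groups, and concludes that "a sample of 60 analysable patients has a power of 95% to detect a significant difference in two-sided formulation and using a Student's t-test". The level of the test is 0.05 and the planning prevalence is 15%. The same section cites 20 to 30% from the literature. It gives no target precision, null value or minimum acceptable value for the AUC or any other accuracy measure.

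Section 9 says that the predictive capacity of the index "will be estimated on the basis of sensitivity, specificity, false-positive and false-negative rates, and the area under the ROC curve". PPV and NPV are not in that list. Section 9 mentions Student's t-test only for the exploratory univariate comparison of heart rate variability parameters.

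**The concern.** A sample size should be justified for the quantity on which the study will be judged. Here the only justification concerns a difference in means, a comparison that section 9 treats as exploratory. A significant mean difference shows that the index is related to chorioamnionitis. It does not show how well sensitivity, the predictive values or the AUC will be known.

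The rationale in section 2 makes the further use of the index depend on confirming the pilot results. A reader of section 8 could take 95% power as assurance that the study can do this. The precision of the AUC and of sensitivity depends mainly on the number of cases, which is about 9 at the planning prevalence. The stated 95% should also follow from the inputs printed beside it, and it does not.

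**Working it through.** **Power as stated**

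Inputs, all from section 8: means 3.82 and 1.18 (difference 2.64), SD 1.7, two-sided alpha 0.05, 60 patients, prevalence 15%. This gives 0.15 × 60 = 9 cases and 51 non-cases.

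- Standardised difference: 2.64 / 1.7 = 1.553.
- Noncentrality: 2.64 / (1.7 × √(1/9 + 1/51)) = 2.64 / 0.615 = 4.30, with 58 degrees of freedom.
- Power from the noncentral t distribution: **98.8%** (normal approximation 99.0%), against 95% stated.

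Other readings of the same inputs:

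- Number of cases random, binomial (60, 0.15), power averaged over that distribution: 97.0%.
- Welch test: 97.4%.
- Mann-Whitney, with efficiency 0.864 to 0.955: 97.5 to 98.5%.
- One-sided test: 99.5%.

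Values near 95% need inputs other than those stated: 6 cases (94.4%), 7 cases (96.7%) or alpha 0.01 (94.5%). On the stated inputs about 45 patients already give 95%.

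**Precision of the AUC with 60 patients**

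The pilot AUC of 0.88 (section 2) is taken as true. The Hanley-McNeil standard error, with m cases and n non-cases, is

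SE² = [A(1 − A) + (m − 1)(Q1 − A²) + (n − 1)(Q2 − A²)] / (mn), where Q1 = A/(2 − A) = 0.7857, Q2 = 2A²/(1 + A) = 0.8238 and A² = 0.7744.

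For 9 and 51: SE² = (0.1056 + 8 × 0.0113 + 50 × 0.0494) / 459 = 0.0058, so SE = 0.076 and the half-width is 1.96 × 0.076 = 0.149.

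| Setting | Cases / non-cases | SE | Half-width | 95% CI |
|---|---|---|---|---|
| 15% prevalence | 9 / 51 | 0.076 | 0.149 | 0.73 to 1.00 (truncated) |
| 20% prevalence | 12 / 48 | 0.067 | 0.130 | 0.75 to 1.00 (truncated) |
| 30% prevalence | 18 / 42 | 0.056 | 0.109 | 0.77 to 0.99 |
| Pilot, assumed split | 10 / 13 | 0.079 | 0.154 | 0.73 to 1.00 (truncated) |

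The protocol reports a lower limit of 0.73 for the pilot. The 10/13 split is an assumption: it is the division of 23 patients that fits the reported sensitivity of 90% (9/10) and specificity of 84.6% (11/13). Appendix 2 is not shown.

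**Precision of the proportions at 15% prevalence (exact Clopper-Pearson intervals)**

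| Measure | This study, 9 / 51 | Pilot, assumed 10 / 13 |
|---|---|---|
| Sensitivity | 8/9: 52 to 100% | 9/10: 55 to 100% |
| Specificity | 43/51: 71 to 93% | 11/13: 55 to 98% |
| PPV | 8/16: 25 to 75% | 9/11: 48 to 98% |
| NPV | 43/44: 88 to 100% | 11/12: 62 to 100% |

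Sensitivity and PPV are no better determined than in the pilot (PPV interval width 0.51 against 0.50). Specificity (0.22 against 0.44) and NPV (0.12 against 0.38) are clearly better. Sensitivity improves with prevalence: 11/12 at 20% gives 62 to 100%, and 16/18 at 30% gives 65 to 99%.

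**Section 5.1 against section 9**

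Both list AUC, sensitivity and specificity. Section 5.1 adds PPV and NPV. Section 9 instead has false-positive and false-negative rates, which in their usual sense are 1 − specificity and 1 − sensitivity and so add no information.

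**The case against.** The strongest defence is that the power error is harmless. The text understates the power, 60 patients satisfy 95% read as a minimum, and no decision changes. This stands: a reader might infer that the study is underpowered, and the figures show the opposite for the t-test. But 95% is printed as the power, not as a floor, and it does not match its inputs.

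Second, the t-test is not unrelated to accuracy. With normal distributions of equal variance, a difference of 1.553 SD implies an AUC of Φ(1.553/√2) = 0.86, close to the pilot's 0.88, so the test amounts to asking whether the index discriminates better than chance. This is fair, but discrimination better than chance is a much weaker statement than a usefully precise AUC or sensitivity.

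Third, a reader might infer that the primary measures as a whole will be no more precise than in the pilot. The documents do not support that. It holds only for the AUC, sensitivity and roughly PPV, only at 15% (the lowest prevalence the protocol mentions), and only on an assumed pilot split. The reported pilot PPV (71.5%) and NPV (95.2%) do not equal 9/11 and 11/12. They fit the reported sensitivity and specificity at about 30% prevalence, so the split remains an inference.

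Fourth, a reader might say that the protocol has three rival primary criteria. It does not. Section 9 does not label its list as primary or withdraw PPV and NPV, so this is a minor mismatch. Reporting several accuracy measures for an estimation aim is also legitimate, and naming a single one would be partly a matter of preference.

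**Conclusion.** The point holds in a limited form and should be fixed, but it is not critical. The sample size in section 8 is not tied to the primary criterion in section 5.1, and this stands whatever a separate SAP contains, because the protocol itself states the justification, for a different quantity. The 95% is wrong as written by about 2 to 4 percentage points, in the conservative direction: 98.8% given exactly 9 cases, 97.0% with a random number of cases. Since inclusion is prospective and the case count is not fixed, 98.8% should not be treated as the one correct value.

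The practical consequence is limited precision for the AUC and sensitivity if prevalence is as low as 15%. It eases at 20 to 30% and does not extend to specificity or NPV. The precision figures take the pilot estimates as true; the comparison with the pilot also relies on the inferred 10/13 split. The omission of PPV and NPV from section 9 is a real but small inconsistency.

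**What to change.** 1. Section 8: give the expected precision of the primary accuracy measures with 60 analysable patients, across 15 to 30% prevalence, as the basis for the sample size. For an AUC of 0.88 the 95% CI is about 0.73 to 1.00 at 15%, 0.75 to 1.00 at 20% and 0.77 to 0.99 at 30%. Sensitivity at 15% is about 52 to 100% and specificity about 71 to 93%. State that these assume the pilot values.
2. Section 8: if the t-test statement is kept, restate its power as about 97 to 99% and label it as power to detect a difference in mean index, not to confirm diagnostic accuracy.
3. Section 9: add PPV and NPV so that the stated analysis covers everything in section 5.1.

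The cost is wording only, with no extra patients. The drawback is that the justification will look less favourable, because it will show how wide the AUC and sensitivity intervals may be at low prevalence.

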## 9. STATISTICAL ANALYSIS

The predictive capacity of the index of episodes of high variation and the uni/multivariate indicator obtained from HRV parameters will be estimated on the basis of sensitivity, specificity, false-positive and false-negative rates, and the area under the ROC curve.

An exploratory univariate analysis of the parameters used to analyse HRV will be carried out. Comparisons of the distributions, means and medians of these parameters in the monitoring blocks associated with histological chorioamnionitis and in the blocks not associated with histological chorioamnionitis will be carried out (Student's *t* test and Mann-Whitney test).

Changes over time in the various parameters measured will be compared between the two populations using a 2-factor repeated time ANOVA (gestational age and chorioamnionitis). The subject effect will be included in the model to take account of the matched nature of the measurements.

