After 34 weeks' amenorrhea (WA), there is no consensus on the appropriate course of action to be taken between expectant care with monitoring or a decision to give birth. However, before 34 WA, the management of preterm PROM consists of expectant care with close maternal-fetal monitoring in a high-risk pregnancy unit of a level appropriate to the gestational age. (15). On the other hand, if signs of chorioamnionitis are detected, the pregnancy should be terminated and the baby should be delivered urgently (16).

The strategies used to reduce the risk of chorioamnionitis in cases of preterm PROM are, on one hand, the systematic prescription of antibiotics and, on the other, close clinical and biological monitoring to detect its

occurrence as early as possible.

However, there is currently no specific marker for the early detection of chorioamnionitis:

- the clinical signs of chorioamnionitis are inconstant, variable, non-specific and usually occur at an advanced stage of infection (uterine contractions, hyperthermia, maternal and/or fetal tachycardia, uterus painful to palpation, foul amniotic fluid). (17).
- the positive predictive value of biological markers used in routine clinical practice is very low, particularly for CRP and hyperleukocytosis, which are the most widely used in France. The measurement of certain cytokines seems promising, but is still experimental and is not the subject of large series. Furthermore, although the sensitivity of these cytokines is interesting, none of them is specific for fetal or intra-amniotic infection (18).

A study carried out at Rennes University Hospital (Appendix 2) has shown for the first time that analysis of fetal heart rate (FHR) variability is a promising avenue of research in this indication.

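### Gestational age is a factor in the ANOVA of changes over time but is not carried into the block comparisons of HRV parameters or the ROC analysis of the secondary HRV indicator

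*Protocol*

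**What the plan says.** Protocol Section 9 names three analyses.

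1. The index of high-variation episodes and the uni/multivariate HRV indicator are judged on "sensitivity, specificity, false-positive and false-negative rates, and the area under the ROC curve". No covariate is mentioned.
2. "An exploratory univariate analysis of the parameters used to analyse HRV will be carried out". This consists of "Comparisons of the distributions, means and medians of these parameters in the monitoring blocks associated with histological chorioamnionitis" and in blocks not so associated, by Student's t and Mann-Whitney tests. Chorioamnionitis status is the only factor.
3. Changes over time are compared "using a 2-factor repeated time ANOVA (gestational age and chorioamnionitis" as the two factors), with a subject effect added.

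Section 5.2 makes the ROC scoring a secondary criterion: it will "assess the diagnostic value of the other HRV analysis parameters selected in the form of either a univariate or multivariate indicator". Section 3.2 sets the matching objective. Section 4.1 admits membrane rupture between 26 and 34 weeks, and Section 7.2 collects recordings from inclusion until birth. Section 7.1 calls the design case-control, and no matching or stratification on gestational age is described. The inclusion visit records "Precise pregnancy dating (obstetric ultrasound performed between 11 WA + 1 day and 14 WA + 6 days"), so gestational age can be worked out for every dated recording.

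**The concern.** Many HRV parameters, such as baseline rate and short-term variation, are absolute levels. If such a parameter changes as the fetus matures, and the two groups are recorded at different gestational ages, a comparison without gestational age attributes part of that maturation to chorioamnionitis. The protocol treats gestational age as a source of variation, since it is a factor in the ANOVA.

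There is a plausible route to a difference between groups. Section 2 describes expectant care before 34 weeks, but "if signs of chorioamnionitis are detected, the pregnancy should be terminated and the baby should be delivered urgently". Women whose infection is recognised may therefore have their last recordings earlier in pregnancy than the others.

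At stake is the second secondary objective. A parameter that only tracks maturity could look like a marker of infection, and a real marker that moves against maturation could be hidden. The AUC of the indicator would then mix discrimination by infection with discrimination by gestational age, which the clinician already knows from the dating scan.

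**Working it through.** **Where gestational age enters**

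| Analysis in Section 9 | Gestational age | Subject effect | Gives AUC, sensitivity, specificity |
|---|---|---|---|
| ROC scoring of index and HRV indicator | not named | not named | yes |
| Exploratory block comparisons | not named | not named | no |
| Repeated-measures ANOVA | factor | included | no |

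The only analysis that accounts for gestational age yields none of the accuracy measures required by Section 5.2.

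**Size.** The protocol gives no figure on this point, so the following is an illustration.

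From the protocol:
- Section 8: 60 analysable women at 15% prevalence, so 0.15 × 60 = 9 cases and 51 non-cases; two-sided 5% level.
- Section 4.1: rupture between 26 and 34 weeks, taken as uniform.
- Section 4.3: delivery within 48 hours excluded, so 2/7 week is added.
- Summary, research duration: average maternal follow-up of 4 weeks. It is given for mothers overall; using it as the non-case interval is an assumption.

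Assumed: exponential intervals, a mean case interval of 1 to 4 weeks, and a correlation r of 0.3 to 0.7 between parameter and gestational age (GA).

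*Closed form.* For a marker that depends only on GA, with groups D standard deviations apart, the null AUC is Φ(rD/√2) and the t-test noncentrality is rD/√(1/9 + 1/51) = rD/0.3615.
- r = 0.2, D = 0.25: AUC 0.51, rejection 5%.
- r = 0.5, D = 0.5: rD = 0.25, noncentrality 0.69, AUC 0.57, rejection 10%.
- r = 0.5, D = 1: noncentrality 1.38, AUC 0.64, rejection 27%.

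*Simulation.* One value per woman and no case effect. GA at last recording = min(rupture + 2/7 + interval, end of recording). Parameter = r(GA − 32)/2.95 + √(1 − r²) × standard normal error. The divisor 2.95 is roughly the standard deviation of GA in the first row below. The slope is held fixed, so the realised correlation is somewhat lower in the other rows. In the 34-week rows, recording ends at 34 weeks or 2 days after rupture, whichever is later.

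T-test false-positive rates, mean case interval 1 week against 4 weeks in non-cases:

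| Recording used; end of recording | Cases younger by | r = 0.3 | r = 0.5 | r = 0.7 |
|---|---|---|---|---|
| Last; 37 weeks | 2.1 weeks | 9% | 17% | 27% |
| Last; 34 weeks | 1.3 weeks | 7% | 10% | 17% |
| Mid-interval; 37 weeks | 1.1 weeks | 6% | 8% | 12% |
| Mid-interval; 34 weeks | 0.65 weeks | 5% | 6% | 8-9% |

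Repeat runs differ by one or two percentage points. Further results:
- First row, mean null AUC in the direction of immaturity: 0.56, 0.60 and 0.65.
- Last recording, 37 weeks, case interval 2 weeks (about 1.3 weeks younger): 7%, 8% and 13%.
- Same, case interval 3 weeks: 5-7%; equal intervals: 5%.
- 18 cases against 42 (30% prevalence), first-row conditions: about 12% and 25% at r = 0.3 and 0.5.
- GA added to the model: about 5% in every setting.

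These rates come from the gestational-age gap alone. With one value per woman, correlation between blocks of the same woman plays no part.

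**The case against.** The case against has five parts.

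*The plan already adjusts.* The ANOVA has gestational age, chorioamnionitis and a subject effect, close to the model one would ask for. This stands for the parameter comparisons: a reader who concluded that Section 9 ignores gestational age would be wrong. It does not reach the ROC analysis, for which the ANOVA gives no result.

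*The block tests are exploratory.* They are labelled so, and a univariate screen is unadjusted by nature. This stands. The label does not extend to the ROC scoring, which serves a stated secondary criterion.

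*The group gap is not shown.* A reader might infer from Section 2 that urgent delivery necessarily makes cases younger. The documents do not support that. The rule is triggered by detected signs, while the groups are defined afterwards by placental histology. Section 2 itself calls the clinical signs inconstant, non-specific and late. Some histological cases will go unrecognised, and some non-cases will deliver early. A gap in the other direction would reverse the bias.

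*The indicator is not fully specified.* That raw parameters are chosen through the block tests and entered unadjusted is an inference; Section 5.2 says only that they are selected. Details may sit in an analysis plan that is not shown. This limits the point to what Section 9 does name: unadjusted tests and an ROC analysis, beside an ANOVA that uses the covariate.

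*The larger rates need strong assumptions.* They need a fourfold difference in interval, a high correlation, and use of the last recording only. The lower rows of the table show how quickly the effect shrinks.

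**Conclusion.** The point holds for the secondary analyses only. Gestational age is in the ANOVA of changes over time but is not carried into the exploratory block comparisons or the ROC analysis of the secondary HRV indicator, and no matching replaces it. If gestational age at recording differs by histological group, those results can partly reflect maturation.

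With assumed case intervals of 1-2 weeks against 4 weeks and r of 0.3-0.7, the false-positive rate lies between about 5% and 27%, depending on when recording ends and which recording is used. It is about 5% if intervals are equal or gestational age is modelled. The documents give neither gestational age by group nor any relation of HRV to gestational age, so the direction of the argument is firmer than its size.

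A reader might extend the point to the primary index. That index is a ratio of a fetus's last two recordings to its own four preceding ones (Section 3.1), which removes much of the difference in maturity between fetuses. No change to it follows from this point.

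**What to change.** In Section 9:

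- Base inference on the HRV parameters on a model with chorioamnionitis, gestational age at recording and the subject effect already planned for the ANOVA. Keep the t and Mann-Whitney results as description.
- For the secondary uni/multivariate indicator of Section 5.2, report alongside the unadjusted figures either a gestational-age-adjusted AUC or the gain in AUC over gestational age alone.
- Leave the primary index and its analysis as they are.

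The cost is a few lines of text and one model term. No new data are needed, because the dating at inclusion gives gestational age at each recording. The downside is one more term to estimate with about 9 cases, and AUCs for the indicator that may be less favourable.
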